## Methods

### Hypotheses

This project is guided by the technology acceptance model (TAM), which theorizes that an ICT’s acceptability is determined by its perceived ease of use and usefulness [31]. It is thus hypothesized that greater perceived usefulness and ease of use of the MI-Coach: ED app will lead to greater use and engagement with the app, and subsequently, improved treatment outcomes. It is also hypothesized that participants will experience an improvement in their motivation to recover from an ED following use of the app. In addition, the app’s acceptability and feasibility will be examined, as well as the possible impacts of other clinical variables (eg, depression, anxiety, BMI, and ED severity) on motivation to recover.

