### Study Design

The current pilot test evaluation follows a naturalistic pre-post design. A pilot test framework was chosen to assess the initial feasibility and acceptability of the app and to identify any potential issues with the study design and delivery format prior to evaluating the app’s efficacy at a larger scale [32]. The MI-Coach: ED app was designed to improve motivation in women-identifying people waiting for formal ED treatment and will be pilot-tested in the province of British Columbia, Canada. Qualitative and descriptive data were collected to determine the acceptability and feasibility of the MI-Coach: ED app.

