Following approaches outlined in previous research [15], the research team then performed iterative content analyses to remove or reframe any references misaligned with ED recovery principles (eg, shifting from weight-centric to motivation-centered goals that explore the individual’s reasons for seeking treatment, and the inclusion of topics such as ambivalence and identification of goals and values relevant to recovery). The overall structure and MI principles used in the original app were retained given their demonstrated effectiveness within an ED context [8]. Throughout this process, informal stakeholder consultations were conducted with ED-specialized clinicians involved in the project, who verified the appropriateness of the revised app content. All video lessons were subsequently refilmed using the University of British Columbia Okanagan’s recording studio and equipment. The new videos featured a clinical psychologist with ED treatment expertise to reduce discrepancies between the original and adapted app content (eg, clinical expertise and years of training). Examples of the MI-Coach: ED interface are provided in Figure 1.

Once the adaptation of app content was completed, a new section was built into the interface of the existing MI-Coach app by technological partners (Resiliens Inc) to house the adapted content. Several components of the base app (ie, assessments, audio tracks, analytics, discussion groups, and communication with the mental health professional) were removed to reduce the scope of the project and to protect participant confidentiality. The final adapted MI-Coach: ED app consisted of seven modules (Multimedia Appendix 2) targeting motivation to engage in ED recovery behaviors (eg, help-seeking, values exploration, and self-acceptance) covering the following topics sequentially: ambivalence and behavior change, self-acceptance and compassionate motivation, exploring possible behavior change goals, sustain and change talk, commitment language, and relapse prevention.

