### Outcomes and Measures

The primary outcomes that will be evaluated are the overall acceptability and feasibility of the MI-Coach: ED (Multimedia Appendix 3)*.* Feasibility will be assessed through attrition rates throughout the study period, frequency of app use, and module completion. Acceptability will be assessed through qualitative and quantitative feedback from participants through semistructured interviews and self-reports. Additionally, exploratory analyses will be conducted regarding the impacts of the MI-Coach: ED app on motivation and associated clinical characteristics.

Self-reported demographic data, including gender identity, age, level of education, ethnicity, and socioeconomic status were collected using Qualtrics, a web-based and secure data collection platform. Additionally, clinical data (ie, weight and height, history of ED treatment, age of ED onset, presence of cognitive difficulties, sensory deficits, history of traumatic brain injury, other mental health comorbidities, and ED waitlist experiences) was collected. The Sick, Control, One, Fat, and Food questionnaire [43], a brief screener that identifies the presence of common ED symptoms, was used to determine eligibility prior to enrollment. Clinical characteristics (ie, eating pathology, recovery motivation, body dissatisfaction, depression, and anxiety symptoms) were evaluated through several self-report questionnaires administered at baseline and posttest, including the Eating Disorder Examination Questionnaire (EDE-Q) [44], the Readiness and Motivation for Change Questionnaire (RMQ) [45], the Body Shape Questionnaire (BSQ) [46], the Patient Health Questionnaire-9 (PHQ-9) [47], and the 7-item General Anxiety Disorder Scale (GAD-7) [48]. Additionally, technological literacy was evaluated at baseline using the Mobile Device Proficiency Questionnaire [49] and the eHealth Literacy Scale [50].

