The subsequent pilot-test portion of the study consisted of a four-week period during which participants used the app in a naturalistic way. Following study completion, participants were compensated CAD $10 (≈US $7.10) for each study portion completed (ie, baseline questionnaire package, onboarding session, posttest questionnaire package, and exit interview), receiving up to CAD $40 (≈US $28.41) through the Tango Card rewards platform. To reduce the impact of possible confounds (eg, financial motivation), participants were informed that their compensation would not be impacted by their app use during the pilot test phase and that there are no minimum requirements for app use. Once the pilot test was completed, a second brief consent form (Multimedia Appendix 5) and posttest questionnaires assessing self-reported clinical features (ie, the EDE-Q, RMQ, PHQ-9, GAD-7, and BSQ) and feedback regarding the app (ie, the adapted TAM-Q and uMARS) were completed. Finally, participants were invited to participate in a videoconferencing-based exit interview to provide additional feedback on their experience with the study author. The semistructured interview guide (Multimedia Appendix 6) was used as an outline to standardize the interview process across participants [52].

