### Statistical Analysis

Prior to analysis, interview audio recordings will be transcribed verbatim by 2 trained research assistants and verified by the primary researcher ([name]). Qualitative interview transcripts will be analyzed using the NVivo software package (version 12; QSR International), to assess in-depth feedback regarding MI-Coach: ED’s feasibility and acceptability. A thematic content analysis will be conducted to analyze the qualitative responses from the open-ended uMARS questionnaire and semistructured interview data using Braun and Clarke’s [36] framework. A bottom-up theoretical approach was used, in which the analysis was driven by the data generated through the semistructured interviews [36,53].

Additionally, quantitative analyses will be conducted using the R statistical package (version 4.2.0; R Core Team). Descriptive analyses of posttest feedback questionnaires, attrition data, and sessions completed will be used to determine the feasibility and acceptability of the MI-Coach: ED app. Means, SDs, ranges, and percentages will be calculated for all descriptive variables (ie, age, ethnicity, BMI, height, and weight), and total and mean scores will be calculated for app acceptability measures. Overall app use (ie, number of modules completed, days that the app was used, assessments and exercises completed, and logins) will be calculated using in-app data provided by Resiliens Inc.

Finally, tests of clinical significance [54] will be used to evaluate changes in clinical presentation across time points. The following categorizations will be used to identify whether change is clinically significant: reliably improved, in which there is reliable change and the clinical cutoff is no longer met; reliably deteriorated, in which there is a reliable change in the disordered direction and the individual’s score falls within the clinical range; and unchanged, in which neither criteria of the Jacobson-Truax method are met [54,55]. Finally, exploratory growth curve analyses will be used to model individual participants’ change trajectories across the 4-week pilot test period [56].

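### The planned growth curve analysis of individual trajectories cannot be supported, because the clinical scales are measured only at baseline and posttest

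*Protocol article*

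**What the plan says.** All places are in the Methods of the protocol article.

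- **Statistical Analysis:** after the reliable-change categories, the plan states that "exploratory growth curve analyses will be used to model individual" trajectories of change over the four weeks of app use. It names no outcome, random-effects structure or constraint on the residual variance.
- **Study Design:** "The current pilot test evaluation follows a naturalistic pre-post design".
- **Outcomes and Measures:** the clinical characteristics "were evaluated through several self-report questionnaires administered at baseline and posttest". The same five scales are listed once before app access and once after it. The interval between them "consisted of a four-week period during which participants used the app in a naturalistic way", and no questionnaire is described within it. Payment is CAD $10 for each of four portions (baseline package, onboarding, posttest package, exit interview), up to CAD $40, which leaves no paid interim assessment.
- **Intervention:** "Several components of the base app (ie, assessments, audio tracks, analytics, discussion groups, and communication with the mental health professional) were removed". Statistical Analysis nevertheless counts completed assessments among the in-app measures of overall use.
- **Hypotheses:** it is expected that "participants will experience an improvement in their motivation to recover from an ED following use of the app".

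**The concern.** An individual trajectory needs enough occasions per person to tell true change from measurement error. With two, each person's line passes through, or is shrunk from, two error-prone points, and nothing in the data says how much of the spread in observed change is real. A fitted slope variance, or a set of individual slopes, would then reflect a software default or an unstated constraint rather than the participants.

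This matters because, besides the reliable-change categories, the growth curve is the only quantitative method that Statistical Analysis names for clinical change. The Conclusions also say that the exploratory analyses will supply preliminary effect sizes for planning a full-scale trial. Results that depend on an arbitrary split of variance should not feed that step.

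**Working it through.** The plan gives no figure for this analysis, so there is nothing to reproduce. The check is one of identifiability.

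**Inputs from the document:** two occasions per scale, four weeks apart, and 30 participants, so at most 60 observations per scale.

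**Model:** y = (b0 + u0) + (b1 + u1)·t + e. The variance parameters are t00 (intercept), t11 (slope), t01 (their covariance) and s2 (residual). Code baseline as t = 0 and posttest as t = 1.

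- Var(y0) = t00 + s2
- Cov(y0, y1) = t00 + t01
- Var(y1) = t00 + 2·t01 + t11 + s2

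There are three equations and four unknowns. Counting the means as well, there are 2 + 3 = 5 moments against 2 + 4 = 6 parameters, so df = -1. The map from variance parameters to the covariance matrix has rank 3 of 4. With 30 people there are 60 random effects for 60 observations. More participants would not help, because the shortage is of occasions.

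Combining the equations gives Var(y1 - y0) = t11 + 2·s2, so t11 = Var(y1 - y0) - 2·s2.

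**Illustration (assumed values):** variance 1 at both visits and covariance 0.6. Then Var(y1 - y0) = 1 + 1 - 2(0.6) = 0.8, t00 = 1 - s2, t01 = s2 - 0.4 and t11 = 0.8 - 2·s2.

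| s2 | t00 | t01 | t11 | t00·t11 | t01² |
|---|---|---|---|---|---|
| 0 | 1.0 | -0.4 | 0.8 | 0.80 | 0.16 |
| 0.1 | 0.9 | -0.3 | 0.6 | 0.54 | 0.09 |
| 0.2 | 0.8 | -0.2 | 0.4 | 0.32 | 0.04 |
| 0.3 | 0.7 | -0.1 | 0.2 | 0.14 | 0.01 |
| 0.4 | 0.6 | 0 | 0 | 0 | 0 |

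Every row is a valid covariance matrix (t00·t11 is at least t01²) and reproduces the same observed moments.

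**Second assumed case:** variances 1.0 and 1.4, covariance 0.6, time in weeks (0 and 4). Here 16·t11 + 2·s2 = 1.0 + 1.4 - 1.2 = 1.2. Residual variances of 0, 0.20, 0.35 and 0.50 give slope variances of 0.075, 0.050, 0.031 and 0.0125, again with identical fit.

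**What remains identified:** every row of the table has Var(y1 - y0) = 0.8. The mean change therefore has the same standard error in each, √(0.8/30) = 0.16 with 30 complete pairs. Only the split between slope and residual variance is undetermined.

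**What would identify it:** three occasions give 3 + 6 = 9 moments against 6 parameters (3 df). With two occasions, only reduced models are identified: a random intercept alone (5 moments, 4 parameters), or a random slope with the residual variance fixed in advance (5 and 5).

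**The case against.** The strongest reply is that the article does not write out a model. An analysis plan that is not shown could specify an identified two-occasion version, and that level of detail is commonly left to such a plan. Part of this stands: it cannot be said that no model would fit. But a random-intercept model gives everyone the same slope, which is not what the sentence promises. Fixing the residual variance from an outside reliability would identify slope variance, and the reliable-change method already needs such a value, but the article does not say it would be used this way. The answer would then rest on the borrowed number: in the example, a shift of 0.1 in s2 moves the slope variance by 0.2. Values near s2 = 0 are implausible for questionnaires, so the practical range is narrower than the table's, but still wide.

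In-app data might hold more time points. The counts of completed assessments conflict with the statement that assessments were removed. As described, though, these are totals of overall use, not repeated clinical scores, and they supply no third clinical occasion. The measures appendix and the flow figure are not shown, but the main text is consistent about two occasions. Unequal intervals between visits could give weak, formal identification through model assumptions, yet the plan states a common four-week period.

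A reader might go further and infer that the motivation hypothesis is left with no valid estimate of mean change. The documents do not support that. The mean time effect is identified, the Abstract states before-after change as an exploratory aim, and the growth curve sentence is not tied to motivation or any other named outcome.

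**Conclusion.** The point holds for individual trajectories and slope variance on the five clinical scales: four variance parameters against three second moments, and no view of curve shape. It assumes a free residual variance and the two occasions that the main text describes.

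It does not extend to mean pre-post change, which stays estimable, or to the primary outcomes of feasibility and acceptability, none of which uses this model. Because the analysis is exploratory and no sample size or decision depends on it, this is a should-fix rather than a must-fix. Exploratory status lowers the stakes but does not make an unidentified quantity estimable.

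**What to change.** Replace the growth curve sentence with the following: for each of the RMQ, EDE-Q, BSQ, PHQ-9 and GAD-7, estimate the mean baseline-to-posttest change with a 95% CI from a two-occasion model with fixed time and an unstructured 2x2 covariance. This keeps participants who have a baseline only. Show individual change as paired plots, and make no claim about trajectories or slope variance.

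Do not describe this model as equivalent to a random-intercept model. The latter forces equal variances at the two visits and a non-negative covariance. With complete pairs and a non-negative covariance the two agree on mean change, but they generally differ when some participants lack a posttest.

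Separately, reconcile the Intervention section, where in-app assessments are removed, with Statistical Analysis, where completed assessments are counted.

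The cost is a few sentences of analysis wording and no new data. The article says that analysis is under way, so the change should be made before results are reported. What is given up is a trajectory claim that the data cannot bear.

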## Results

The MI-Coach: ED app has been developed and is available for download and use. Recruitment was initiated in November 2022 and terminated in May 2024. Data analysis is currently underway, and we anticipate reporting results through peer-reviewed academic publications in May 2025.

## Discussion

### Anticipated Results

This study aimed to evaluate the feasibility and acceptability of MI-Coach: ED, an app designed to support motivation for ED recovery among individuals on treatment waitlists. It is anticipated that the intervention will be feasible to implement, with a high rate of participant engagement with the app, and that MI-Coach: ED would be perceived as an acceptable and useful tool for supporting motivation during the waitlist period. Prior research suggests that digital mental health interventions targeting ED populations are generally acceptable and feasible to users, particularly when they incorporate evidence-based therapeutic principles such as MI [15,28]. Additionally, app-based self-help interventions have demonstrated high engagement rates, which MI-Coach: ED was designed to include [23,27]. Furthermore, we anticipate that exploratory analyses will demonstrate preliminary improvements in motivation and ED-related symptoms following app use, given findings that brief MI-based interventions can enhance motivation for change, improve treatment engagement, and reduce ambivalence in ED populations [8,14,16,17]. As motivation is a key predictor of ED treatment outcomes [11], even small gains during the waitlist period could have meaningful clinical implications.

### Conclusions

Individuals with EDs face substantial barriers to accessing appropriate care, despite their urgent need for treatment [37,57,58]. Though both MI and app-based interventions have been suggested as ways to support treatment-seeking ED patients, in isolation, these interventions may not adequately address treatment barriers. For example, in-person MI interventions may be inaccessible to individuals in rural and remote locations, and interventions currently delivered through apps have limited evidence to support their efficacy [24]. As such, this study aims to simultaneously address individual and structural treatment barriers by developing and pilot-testing an MI-based app intervention for women on waitlists for ED treatment.

Providing app-based interventions to individuals who are waiting for ED treatment has the potential to improve treatment outcomes and represents a largely barrier-free, positive-approach method of addressing the growing problem of wait times for mental health care. Although this pilot study focuses on a modest sample, existing intervention frameworks and ED-focused digital interventions demonstrate how pilot studies can be used to guide the adaptation and evaluation of novel interventions through large-scale clinical trials [15,20,28]. For example, collecting and implementing end user feedback prior to formal efficacy testing has been suggested to ensure that the final intervention is used by the targeted population [28]. Furthermore, exploratory analyses on motivation and ED-related symptoms will help identify meaningful clinical outcome measures and establish preliminary effect size estimates to guide the design and power calculations for a full-scale randomized controlled trial. Additionally, by collecting demographic and digital literacy data, this study will provide insights into the app’s accessibility across diverse populations and inform potential adaptations to increase inclusivity. Future evaluations will also aim to follow participants into formal psychological treatment to assess the long-term clinical impact of pretreatment MI interventions.

Given that prior research has demonstrated that multimodal recruitment modalities can enhance sample diversity, improve engagement, and ensure the inclusion of individuals with varying levels of symptom severity in digital intervention studies [38], data collected through this pilot study will be particularly valuable in refining future participant engagement strategies. In this regard, feasibility data collected from this study (including recruitment and retention rates, participant engagement with the app, and qualitative user feedback) will directly inform refinements to MI-Coach: ED and recruitment methods for subsequent large-scale efficacy evaluations, ensuring that the intervention is optimally structured for broader implementation. For example, future studies may continue to use a multipronged approach, such as the use of social media campaigns to supplement clinician referrals [38], and partnerships with provincial authorities may be expanded to integrate study recruitment directly into clinical workflows given their success in prior research [59]. As such, this pilot study serves as a crucial step in optimizing MI-Coach: ED for large-scale implementation and has the potential to provide tangible psychological support to its participants while contributing to the reconceptualization of ED service delivery.

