Despite preliminary findings suggesting that apps may be an acceptable means of delivering ED services, there is a paucity of effective, evidence-based apps available for use [24-27]. Most publicly available app interventions are based on CBT and behavioral self-monitoring principles but demonstrate limited efficacy compared to traditional delivery methods [24,28]. However, considering the accessibility of apps and their wide adoption in various health and social contexts [29], they may be an effective mode of delivery for pretreatment MI contexts. Help-seeking individuals waiting for formal services likely do not have access to in-person treatment options, despite their urgent need for services. Further, as they have not yet started formal ED treatment, receiving a pretreatment MI intervention may significantly improve treatment outcomes. For example, such interventions may increase motivation to stay on the waitlist and adhere to treatment once services are received [30]. An app-based MI intervention thus has the potential to simultaneously address structural and individual treatment barriers. Despite the potential benefits, to date, no research has investigated the use of app-based MI pretreatment interventions for EDs.

The proposed study aims to adapt and pilot-test MI-Coach, a widely available app-based MI platform, for individuals on ED treatment waitlists. Created by Resiliens Inc, MI-Coach is an evidence-based self-help app developed in collaboration with a registered clinical psychologist. The app was adapted for use within an ED pretreatment context. Furthermore, this will be the first study to investigate whether an app-based MI pretreatment intervention improves clinical symptoms, motivation for treatment, and openness to change for individuals while they wait for ED treatment.

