### Study Population

#### Sample Size Estimation

Given the focus of this study on the acceptability and feasibility, rather than the efficacy, of the MI-Coach: ED app, formal analytic methods were not used to estimate the prehoc sample size. In keeping with previous feasibility studies in the ED field [14,33,34] and pilot study guidelines, which suggest that modest sample sizes based on the pragmatics of recruitment are sufficient when evaluating the processes, feasibility, and preliminary acceptability of novel interventions [32,35], a sample size of 30 participants was selected, recruited while they wait for ED services and treatments in British Columbia, Canada. Additionally, it was determined that qualitative interviews would be conducted with interested participants on a rolling basis until thematic saturation is reached [36].

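### Effect sizes from this 30-person one-arm pre-post pilot do not estimate a between-arm effect, so they are a poor basis for powering the later randomized trial

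*Protocol article*

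**What the plan says.** All places are in the protocol article.

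- **Discussion, Conclusions.** The exploratory analyses of motivation and eating disorder symptoms are meant to help choose outcome measures and to "establish preliminary effect size estimates to guide the design and power calculations for a full-scale randomized controlled trial". The paragraph acknowledges a modest sample. It does not mention the missing control group.
- **Study Design.** "The current pilot test evaluation follows a naturalistic pre-post design". There is no comparison arm.
- **Sample Size Estimation.** "a sample size of 30 participants was selected", and "formal analytic methods were not used to estimate the prehoc sample size". The reason begins "Given the focus of this study on the acceptability and feasibility, rather than the efficacy".
- **Outcomes and Measures.** Clinical characteristics are "evaluated through several self-report questionnaires administered at baseline and posttest". The app is used for four weeks in between. The clinical analyses are labelled exploratory, but the section describes them as concerning the app's impacts.
- **Introduction.** "this will be the first study to investigate whether an app-based MI pretreatment intervention improves clinical symptoms, motivation for treatment, and openness to change". The same section reports that delay in treatment is associated with lower motivation before treatment.
- **Anticipated Results.** The authors expect preliminary improvements in motivation and symptoms after app use.

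**The concern.** A parallel-group trial is powered on the difference between arms. A change within one arm is a different quantity. It is the sum of any app effect, whatever would have happened over four weeks on a waitlist, regression to the mean in people who enrolled while seeking help, and the effect of who returns the posttest questionnaires. Without a control group these parts cannot be separated.

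The article also uses its lack of an efficacy aim to justify having no sample size calculation, and then gives the same 30 people the task of supplying an efficacy parameter. At stake is the size of the next trial. If the pilot figure is too high, that trial will be too small. If it is too low, that trial will be larger than needed, or a useful app may be dropped. A pre-post gain may also be read as caused by the app.

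**Working it through.** **Nothing to reproduce.** The 30 was chosen pragmatically. The article gives no alpha, power, effect size, SD or dropout rate, and no size for the later trial. The effect inputs below are therefore assumptions. I use two-sided 5% and 80% power.

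**Step 1: what is estimated.** Write the mean pre-post change as D = A + W, where A is the app effect and W is everything else (waitlist change, regression to the mean, selective completion). The randomized trial needs A. The pilot observes only D. This step needs no numbers. W may have either sign: natural improvement would make D too large, while motivation that falls during the wait, as the Introduction suggests, would make D too small.

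**Step 2: precision of D.** Take an observed standardized change d = 0.4 (change divided by the SD of change, normal differences). Inverting the noncentral t with t = d√n and n − 1 degrees of freedom gives:

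| Completers | 95% CI for d = 0.4 |
|---|---|
| 30 | 0.02 to 0.77 |
| 24 (assumed 20% loss) | −0.02 to 0.81 |
| 20 (assumed) | −0.06 to 0.85 |

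**Step 3: put this into a two-sample calculation, as a planner would.** Per-arm n ≈ 2(1.960 + 0.842)²/d² = 15.70/d². The exact t-test adds one or two:

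- d = 0.77: 15.70/0.593 = 26.5; exact 28 per arm.
- d = 0.4: 15.70/0.16 = 98.1; exact 100 per arm.
- Lower limit with 30 completers, unrounded 0.0246: about 26,000 per arm, which is finite but not practicable. With 24 or 20 completers the lower limit is below zero and no trial size corresponds to it.

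**Step 4: effect of having no control.** Suppose the true between-arm effect is a share s of the observed 0.4. The required size scales as 1/s²:

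| s (assumed) | Between-arm effect | Needed per arm | Power of a trial with 100 per arm |
|---|---|---|---|
| 1.25 | 0.5 | 64 | 94% |
| 1 | 0.4 | 100 | 80% |
| 0.75 | 0.3 | 176 | 56% |
| 0.5 | 0.2 | 394 | 29% |

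The first row is the case in which motivation would have fallen without the app.

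**Step 5: how often sampling error alone mis-sizes the trial.** In 200,000 simulated pilots of 30 with no bias (s = 1), the planned size was off by two-fold or more, in either direction, in 58%, 38% and 20% of runs for true d of 0.3, 0.5 and 0.8. It was off by three-fold or more in 38%, 17% and 5%.

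**The case against.** The claim is one sentence in the Discussion. It calls the estimates preliminary and says that they will guide planning. It fixes no future sample size and sets no rule for analysing this pilot. Feasibility and acceptability are the primary outcomes, are analysed descriptively and are unaffected. A feasibility study may carry exploratory clinical outcomes, and the article labels them so. The Introduction poses improvement as a question, not a result. The article also already names recruitment, retention and engagement as inputs to later efficacy work. All of this stands, and it limits how much weight the point can bear.

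A reader might infer several stronger things that the document does not support:

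- **That the later trial would be mis-sized several-fold.** The multiple depends on the true effect and on the share due to the app, and neither is given. With no bias and a true change of 0.8, a three-fold error occurs in only 5% of runs.
- **That it would probably be underpowered.** This assumes that people on the waitlist improve without the app. The article's own remark on delay and motivation points the other way.
- **That using a change score inflates the effect by a known factor.** The ratio of change divided by its own SD to change divided by a single-time-point SD is 1/√(2(1 − r)) when the two time-point SDs are equal. That is 1.58 at r = 0.8, but 1.00 at r = 0.5 and 0.85 at r = 0.3. The article does not say which standardization it will use.

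What the objection does not answer is that calling an estimate preliminary conveys imprecision. It does not turn a within-group change into a between-group effect.

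**Conclusion.** The point holds in a limited form. The article states a use for its data that a one-arm design cannot support, whatever the numbers turn out to be. The sample was also exempted from formal sizing because efficacy was not the aim. Under an assumed observed change of 0.4, sampling error alone spans about 28 per arm to an impractically large trial. A further assumption that half the change is due to the app moves the requirement from about 100 to about 394 per arm. These figures illustrate what could happen and do not predict it. The later trial could be badly mis-sized in either direction, and the pilot has no means of showing which. The validity of the pilot's own primary results is not in question.

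**What to change.** 1. In the Conclusions, delete the statement that the pilot will establish effect sizes for power calculations.
2. State instead that it will supply the SDs of the clinical outcomes (the RMQ and EDE-Q in particular), their pre-post correlation, the posttest completion rate and the recruitment rate, each with a 95% CI. The interval matters even for an SD: with 30 completers it runs from about 0.80 to 1.34 times the estimate, and since 1.34² = 1.8, the upper limit implies about 1.8 times the sample size for a fixed raw difference.
3. Say that the target difference for the randomized trial will come from a minimally important between-group difference or from controlled evidence.
4. In the Introduction, Outcomes and Measures, and Anticipated Results, describe pre-post results as change observed during app access, without attributing it to the app.

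The cost is a few sentences and some summaries of data already collected. The Results section says analysis is still under way, so the results report can follow this. The downside is a less ambitious claim.
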